# Does a colour-coded blood pressure diary improve blood pressure control for patients in general practice: The CoCo trial

**DOI:** 10.1186/1745-6215-11-38

**Published:** 2010-04-14

## Abstract

**Background:**

Insufficient blood pressure control is a frequent problem despite the existence of effective treatment. Insufficient adherence to self-monitoring as well as to therapy is a common reason. Blood pressure self-measurement at home (**H**ome **B**lood **P**ressure **M**easurement, **HBPM**) has positive effects on treatment adherence and is helpful in achieving the target blood pressure. Only a few studies have investigated whether adherence to HBPM can be improved through simple measures resulting also in better blood pressure control.

**Objective:**

Improvement of self-monitoring and improved blood pressure control by using a new colour-coded blood pressure diary.

**Outcome:**

Primary outcome: Change in systolic and/or diastolic blood pressure 6 months after using the new colour-coded blood pressure diary.

Secondary outcome: Adherence to blood pressure self-measurement (number of measurements/entries).

**Methods/Design:**

Randomised controlled study.

Population: 138 adult patients in primary care with uncontrolled hypertension despite therapy. The control group uses a conventional blood pressure diary; the intervention group uses the new colour-coded blood pressure diary (green, yellow, red according a traffic light system).

**Expected results/conclusion:**

The visual separation and entries in three colour-coded areas reflecting risk (green: blood pressure in the target range ≤ 140/≤ 90 mmHg, yellow: blood pressure >140/>90 mmHg, red: blood pressure in danger zone > 180 mmHg/>110 mmHg) lead to better self-monitoring compared with the conventional (non-colour-coded) blood pressure booklet. The colour-coded, visualised information supports improved perception (awareness and interpretation) of blood pressure and triggers correct behaviour, in the means of improved adherence to the recommended treatment as well as better communication between patients and doctors resulting in improved blood pressure control.

**Trial registration:**

ClinicalTrials.gov ID NCT01013467

## Background

Arterial hypertension is the most common cardiovascular risk factor throughout the world and guidelines for the management of hypertension underscore the need for strict blood pressure (BP) control to decrease the risk of morbidity and mortality in hypertensive patients [1,2]. Despite the available evidence that even mild hypertension is linked to a considerably higher cardiovascular risk, many patients do not reach the target blood pressure under treatment [3].

In Switzerland every seventh adult is affected, only half of them receive treatment. Of those patients treated, which cost the health system in Switzerland over CHF 435 million in 2005 [4], only one-eighth [5] reaches appropriate blood pressure control.

An important factor in achieving targets in the management of hypertension is patient adherence to treatment [6]. A plethora of data exists regarding adherence in the treatment of hypertension [7-12].

A review on how to reach targets in the treatment of diabetes patients in primary care showed that interventions with the greatest positive effect were complex and should include activities which change the behaviour of doctors, changes to practice organisation, expansion and provision of information and educational programmes for patients [13]. The measures to promote adherence in such programmes are the combination of patient information, promoting and supporting self-monitoring support through regular monitoring and inquiries by telephone, social support as well as treatment plans tailored to the individual [14]. Most of these measures require time and personal effort for training and follow-up, which is not easy to implement in the everyday practice life.

With a chronic illness as hypertension the role of the patient changes. The patient is central to efforts to monitor and control the illness to the best possible extent. Knowledge about illness and treatment is the basis, but in particular behaviour strategies are necessary to achieve the best possible long-term control. Our study focuses on patient-related factors as the central condition for improved treatment adherence [15].

Blood-pressure self-measurement at home (HBPM) is an established and evidence-based behaviour measure, which is recommended in guidelines on the treatment of hypertension and which has been shown to improve knowledge about treatment and also adherence to treatment with medication by about 20% [16-19]. Until now only few studies investigated the use of a simple practice tool in hypertensive patients to improve self-monitoring and adherence to HBPM considering its possible effect on blood pressure. We therefore aim to investigate the effect of a colour coded blood pressure diary following a traffic light system (green, yellow, red) on adherence to self-measurement and blood pressure monitoring.

### Hypothesis

The colour-coded blood pressure booklet improves adherence to self-monitoring (higher number of HBPM) and leads to improved blood pressure control.

We are assuming that the colour-coded tool supports adequate patient behaviours by improving awareness and interpretation of blood pressure control. It also might support better patient-doctor communication which is a central aspect for treatment adherence and improved blood pressure control.

## Methods/design

A two-armed study randomised and controlled at patient level. The intervention group will receive a new colour-coded blood pressure booklet, the control group a standard blood pressure record booklet without colour coding. The measuring period for both groups is 6 months (figure 1).

**Figure 1 F1:**
[figure not shown]
**Study flow chart**.

### Inclusion criteria for general practitioners

General practitioners will be invited to join the study via letters sent by post and information sessions. Any general practitioners who provide basic medial care with a workload of at least 20 hours per week are entitled to participate in the study.

### Inclusion criteria for patients

• Age >18 years

• BP > 140/90 mmHg

Two consecutive measurements carried out in the practice

(measured by the general practitioner or practice assistant at the start of the study; both measurements must be greater that 140/90 mmHg with the second measurement qualifying for inclusion.

• Unchanged anti-hypertension treatment for one month before inclusion

• Patient able to measure blood pressure at home

• Written informed consent

### Exclusion criteria

• Blood pressure reading over 180 mmHg systolic and/or 110 mmHg diastolic.

• Serious general or psychological illness (malignant tumours, serious depressive episodes or evidence of dementia).

• Insufficient knowledge of the German language for instruction and blood pressure recording with a booklet.

All patients will be asked consecutively about participating in the study and they will be handed an information sheet. All patients who have been approached will be included in a list containing the blood pressure booklet code which will be passed on to the study centre. The list remains in the practice so that the study leaders only have anonymous access to the patient data. However, in the practice it is possible to link the blood pressure record book with the medical file of the patient so that all the clinical data is available. Any patients who have been approached and have declined to participate will be included in a list in order to carry out a non-responder analysis of patients with regard to socio-demographic and clinical data.

#### Sample Size

Case number calculation and power analysis were carried out on the basis of the expected effect for systolic blood pressure. With an alpha of 0.05 and a power of 0.9 (one-sided test) this means that 138 patients are required in order to be able to show a clinically relevant blood pressure difference of 7 mm Hg systolic with a standard deviation of 14 mmHg between the groups. Assuming a dropout rate of 20% this means that at least 166 patients are required.

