#### Analysis

At the end of the study the list with the booklet codes as well as the code, generated out of the patients' name and his birthday will be send to the study centre. In the study centre, all received questionnaires and lists will be scanned electronically and a TIF-file will be generated to avoid data manipulation. The data will be directly exported in the statistic program (STATA, version 9).

Descriptive statistics: average value with +/- 1 SD and median values of the average blood pressure readings for both groups. In accordance with the normal distribution test it will be decided whether parametric or non-parametric tests are to be applied. Treatment group comparisons for categorical data will be done with the χ^2 ^test. For continuous variables, comparisons between treatment groups were done with *t *tests.

Primary outcome: difference (t2-t0) between the systolic blood pressure average readings from the practice measurement. All patients will be analysed in accordance with the „intention-to-treat” approach and the latest available measurement will be used (last- observation carried forward). When interventions are provided via GPs, one should be aware of a cluster effect. We decided to perform a randomisation on the patient's level since the effect mediated by the GP on the intervention is assumed to be small. Nevertheless, we will account for that and include the factor "Practice" as a random effect in the analysis.

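### The 20% dropout allowance is added to 138 instead of divided out, so 166 randomised patients cover about 17% dropout, a small error in a stated figure

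*Protocol article*

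**What the plan says.** The Sample Size section of the protocol article gives the calculation in two steps.

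- Base requirement: "With an alpha of 0.05 and a power of 0.9 (one-sided test) this means that 138 patients are required", for "a clinically relevant blood pressure difference of 7 mm Hg systolic" "with a standard deviation of 14 mmHg between the groups".
- Dropout allowance: "Assuming a dropout rate of 20% this means that at least 166 patients are required".

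The Methods/Design paragraph of the abstract gives one number only: "Population: 138 adult patients in primary care with uncontrolled hypertension despite therapy". It does not mention 166, and it does not say whether 138 counts patients randomised or patients completing.

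The Analysis section plans an intention-to-treat comparison in which "the latest available measurement will be used (last- observation carried forward".

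**The concern.** A dropout rate is normally a share of the patients randomised. To have a required number left after a loss of 20%, that number is divided by 0.8. Multiplying it by 1.2 gives a smaller total, and 166 looks like the product of that multiplication. If so, the section presents 166 as a sufficient minimum although it does not meet the section's own conditions. At stake is whether the stated combination of 166 patients, 20% dropout and 90% power holds together. A side issue is that a reader of the abstract cannot tell what kind of number 138 is.

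**Working it through.** **Inputs.** All are from the Sample Size section except the allocation ratio: difference δ = 7 mmHg; standard deviation σ = 14 mmHg; one-sided α = 0.05; power 0.90; dropout 20%. The article describes two arms but states no ratio. I assume 1:1, which reproduces the stated 138.

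**Step 1. Reproduce 138.** Normal approximation, per arm:

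n = 2 (z₀.₉₅ + z₀.₉₀)² σ² / δ² = 2 × (1.645 + 1.282)² × 14² / 7² ≈ 68.5, so 69 per arm and 138 in total.

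This matches exactly. The two-sided version gives 85 per arm, 170 in total, so 138 is the one-sided figure, as the section says.

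**Step 2. Reproduce 166.**

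- Multiplying: 138 × 1.2 = 165.6, so 166. This is the stated figure.
- Dividing: 138 / (1 − 0.20) = 172.5, so 173, or 174 if the arms are to be equal.

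**Step 3. What 166 delivers.**

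- Completers at 20% dropout: 166 × 0.8 = 132.8, about 133. This is 5 fewer than 138.
- Dropout rate that leaves 138: 1 − 138/166 = 16.9%.
- Shortfall against the divided figure: 173 − 166 = 7 patients, about 4%.

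**Step 4. Effect on power** (one-sided 5%, δ/σ = 0.5, completers only).

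| Completers | t-test | Normal approximation |
|---|---|---|
| 138 | 0.899 | 0.902 |
| 132.8 (about 133) | 0.889 | 0.892 |

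The loss is about one percentage point by either method.

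**The case against.** The strongest reply is that the consequence is negligible. One point of power is well inside the uncertainty of a planning assumption such as a 20% dropout rate, and the section calls 166 a minimum, so it does not cap recruitment there. Both remarks are right. They limit the importance of the point, but they do not make 166 the correct minimum for 20% dropout.

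A second reply is that carrying the last observation forward keeps dropouts in the analysed set, so 133 is not the number analysed. That is correct: 133 must be called completers, and 89% is the power of a completer comparison. The planned analysis could have higher or lower power, depending on what is carried forward. A patient lost before the three-month visit, for instance, would contribute a change of zero. This still does not rescue 166. If dropouts counted fully, no inflation would be needed and 138 would do. If they count as lost, 173 is needed. Neither reading gives 166.

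A third reply is that multiplying by 1.2 is a common shortcut. If 20% was meant as a share of the 138, the text should say so, and the dropout rate among those randomised is then about 17%.

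Three stronger readings are tempting, and the article does not support them.

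- A reader might infer two competing recruitment targets. The Sample Size section gives both numbers and how they relate, and no passage says to stop at 138. The abstract repeats the figure before the dropout allowance without a label.
- A reader might go on to work out that 138 enrolled with 20% lost leaves about 110 completers and about 83% one-sided power. That scenario contradicts the explicit minimum of 166 and says nothing about the plan as written.
- A reader might quote two-sided power of about 82% at 133 completers as the damage. With 138 completers the two-sided figure is already about 83%, so nearly all of the drop from 90% comes from sidedness and not from the dropout step.

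**Conclusion.** The point stands as a small arithmetic error in a stated figure. On the plan's own inputs, 166 randomised patients do not leave 138 after 20% dropout. They leave about 133 completers, with one-sided completer power of about 89% against the planned 90%, and they cover about 17% dropout. No design feature or conclusion depends on it.

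This rests on 1:1 allocation, on 20% being a share of those randomised, and on the simple two-group comparison behind the stated sample size. That comparison includes neither carried-forward values nor the practice random effect that the Analysis section plans. The abstract's 138 is an unlabelled number and needs only a label.

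**What to change.** In the Sample Size section, choose one of the following.

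- Keep 166 and state that it allows for about 17% dropout.
- Keep 166 and 20%, and state that about 133 patients would then complete, with about 89% one-sided power on completers. Add that the planned last-observation-carried-forward analysis retains dropouts, so its power may differ.
- If 138 completers after 20% dropout are to be kept, state 173 to be randomised (174 for equal arms).

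In the abstract, describe 138 as the number required before the dropout allowance, and give the number to be randomised beside it.

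The first two options and the abstract change cost wording only. The third costs 7 more patients, or 8 with equal arms.

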#### Randomisation

The randomisation (colour-coded vs. conventional blood pressure booklet) will take place at patient-level and will be carried out centrally by the study centre. We will draw up a randomising list by computer (ralloc command of Stata software for Windows, Version 9). The blood pressure record booklets will be distributed on the basis of this list in consecutively numbered opaque envelopes. The opaque envelopes will be given to the practices in numerical order. They can not be resealed. GPs are asked to notice the number (code) of the booklet (colour-coded or normal) on a list together with the name and birthday of the patient and generate a code out of this data. This list will remain in the practice and is just for the purpose to be able to link the booklets with the patients name and therefore the patients' medical file. The study centre will receive a list with the generated code of the patient and the distributed booklet. So, the linkage to the name and medical file is only possible with the list held by the GP. Opened but not used envelopes have to be noticed in the list as used ones and marked as "not distributed". The practices will each receive four envelopes in which there will either be a colour-coded or a standard record booklet. The patients will be included consecutively and the doctor will open one envelope after the other in the order of the envelope numbers. In practice number one envelopes 1-4 will be opened consecutively, in practice number two envelopes 5-8 etc. This central randomisation means that the concealment of random allocation is ensured.

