### Blinding

Blinding of the general practitioners regarding group identity is not possible. Patients do only know that different types of blood pressure record booklets are being distributed, but they do not know in detail what the difference between the booklets is.

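### An unblinded GP opens the envelope and may log it as not distributed, but the protocol does not say that the patient concerned stays in the randomised set, and only the allocation list is central

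*Protocol article*

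**What the plan says.** The Randomisation section of the protocol article describes a list generated by computer at the study centre. From there the procedure is local. On the envelopes it says: "The blood pressure record booklets will be distributed on the basis of this list in consecutively numbered opaque envelopes", and "They can not be resealed". On supply: "The practices will each receive four envelopes in which there will either be a colour-coded or a standard record booklet". On use: "The patients will be included consecutively and the doctor will open one envelope after the other in the order of the envelope numbers". On envelopes that are opened but not handed over: "Opened but not used envelopes have to be noticed in the list as used ones", with a mark showing that the booklet was not given out. The section concludes: "This central randomisation means that the concealment of random allocation is ensured".

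The Blinding section adds: "Blinding of the general practitioners regarding group identity is not possible".

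The study centre receives the generated patient code together with the booklet that was handed out (Randomisation). The Analysis section dates the sending of this list to the end of the study. It also commits to analysing all patients by intention-to-treat, with the last available reading carried forward.

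**The concern.** The person who decides whether to complete a patient's enrolment is also the person who opens the envelope and sees the arm. The protocol provides a recorded outcome in which the envelope has been opened and no booklet is given. It gives no reasons for which this is acceptable and does not say what becomes of the patient.

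If a GP opens an envelope for a consented, eligible patient and the patient then does not proceed, that is a post-randomisation exclusion made with knowledge of the arm. Should such exclusions differ between arms in number or in type of patient, the arms are no longer comparable as randomised. Neither carrying the last observation forward nor the practice random effect repairs this, because the patient may contribute no data at all.

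The sentence on concealment adds to the problem. It credits a central step, and that step ends once the list exists. A reader could conclude that no further safeguard is needed at the point where allocation actually takes place.

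**Working it through.** **Step 1: the text, side by side.**

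- *Who reveals the arm:* the GP, in the practice (Randomisation), unblinded (Blinding).
- *What must happen first:* written consent and two qualifying practice readings are conditions of inclusion (Inclusion criteria for patients), and information and consent come before participation (Patient informed consent). None of these sections places them before the opening of the envelope. The Secondary end point section dates the first data supply to randomisation, which does not settle the order either.
- *What happens to an unused envelope:* it is spent and logged. No reason, no follow-up of the patient and no analysis status are given.
- *Who is analysed:* all patients, by intention-to-treat (Analysis). The act that makes someone a randomised patient is not defined, so a patient whose booklet was not handed over is neither clearly in nor clearly out.
- *What is central:* list generation and envelope preparation. The assignment of a given patient is not.

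**Step 2: reproduce the planned size, to fix the scale.** Inputs from Sample Size: difference 7 mmHg, SD 14 mmHg, one-sided alpha 0.05, power 0.9. Equal arms are assumed, as the ratio is not stated.

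n per arm = 2 × (1.645 + 1.282)² × 14² / 7² = 68.5, rounded up to 69. The total is 138, which matches the protocol. This point disputes no figure in the plan.

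**Step 3: illustrate what selective loss could do.** The documents give neither input below; both are assumptions.

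- f = share of one arm lost after opening, 5% to 20% (of 69 patients, about 3 to 14).
- D = difference in mean systolic change between lost and retained patients of that arm, 5 to 14 mmHg.

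Bias in the between-arm difference = f × D.
SE = 14 × √(1/69 + 1/(69 × (1 − f))).
One-sided type I error, if the bias favours the intervention = 1 − Φ(1.645 − f × D / SE).

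| f | D (mmHg) | Bias (mmHg) | Share of 7 mmHg | Type I error (nominal 0.05) |
|---|---|---|---|---|
| 5% | 5 | 0.25 | 4% | 0.062 |
| 5% | 14 | 0.70 | 10% | 0.088 |
| 10% | 7 | 0.70 | 10% | 0.087 |
| 10% | 14 | 1.40 | 20% | 0.142 |
| 20% | 5 | 1.00 | 14% | 0.106 |
| 20% | 14 | 2.80 | 40% | 0.296 |

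For the last row: SE = 14 × √(1/69 + 1/55.2) = 2.53; 2.8 / 2.53 = 1.11; 1 − Φ(1.645 − 1.11) = 0.30. The calculation ignores clustering by practice. Bias in the other direction would cost power instead. If losses are unrelated to prognosis, D is zero and so is the bias.

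**The case against.** Much of the case on the other side stands.

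- **The log is an accountability rule.** With non-resealable envelopes opened in number order, it stops an unwanted allocation being passed to the next patient. Nothing in it authorises dropping a patient by arm, and an envelope opened by mistake fits the wording equally well. One can even read it as asking for the same list entry, patient details included, as for a used envelope. On that reading a link to the patient exists in the practice, but follow-up and analysis status remain open.
- **Discards can be counted by arm.** The centre holds the randomisation list, each practice has four known consecutive numbers, and the Exclusion criteria section has approached patients listed and decliners kept for a non-responder analysis. This allows detection, but the Analysis section brings the list to the centre only when the study is over, too late to recover outcomes.
- **Concealment and later exclusion are different things.** Concealment means not knowing the next assignment before the patient is committed. Opaque, numbered, non-resealable envelopes opened in order address that. Loss after opening is a separate problem.

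Two stronger readings are tempting and not supported. A reader might infer that intention-to-treat is broken. The Analysis section commits to it, and silence on undistributed cases is not exclusion of them. A reader might also infer from the packs of four that GPs can predict allocations. With fixed blocks of four aligned to the packs, the fourth would always be known and the third in one pack of three, so 1 + 1/3 = 1.33 of 4, or 33%. But the article states no block size, and an article may leave that to the full protocol, so no such figure can be claimed.

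That the GP also takes the practice readings is a question of unblinded assessment and adds nothing here.

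**Conclusion.** The point holds in a limited form. As written, an unblinded GP can see the arm, and the envelope can end as not distributed without any statement that the patient concerned is randomised, followed and analysed. Post-allocation exclusion is possible; the documents do not show that it is intended or that it would be frequent. The claim that central randomisation ensures concealment is stronger than the described procedure supports. What protection there is comes from the envelopes.

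The size cannot be read from the documents. The range of 0.25 to 2.8 mmHg, with one-sided type I error of about 0.06 to 0.30, rests wholly on the assumed f and D and on losses confined to one arm. It shows that modest selective loss would matter against a 7 mmHg target, not that it will occur.

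This is more than omitted detail. Envelope handling is a practice procedure that the article does set out, and no analysis plan can recover patients who were never followed. It should be changed, and the change is nearly free.

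**What to change.** 1. Before an envelope is opened, have the practice record consent, eligibility and the t0 readings on its list, and write the patient code and date on the sealed envelope.
2. Define opening of the envelope as the moment of randomisation.
3. Follow every patient for whom an envelope was opened, within the consent given, and keep them in the intention-to-treat set whether or not the booklet was handed over. Follow-up matters: with only a t0 reading, last observation carried forward would enter a change of zero.
4. Keep the log of undistributed envelopes. Report these by arm with reasons, and list separately any opened in error with no patient assigned.
5. Reword the concealment sentence to credit the sealed, opaque, consecutively numbered envelopes opened in order, not central randomisation.

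The cost is one or two extra lines on a list and an instruction leaflet that practices already use. No visits or staff are added.
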